#### Secondary outcomes

Psychometric tests to assess therapy expectation: The tests will be administered at four points in time (T1: before therapy, T2: in week 2 of therapy, T3: in week 3 of therapy, T4: after therapy).

Treatment Expectation Questionnaire (TEX): In this questionnaire, study participants are asked to self-assess their expectations for a treatment in 15 questions on a scale of 1–10 [33].

Generic rating for treatment pre-Experiences, treatment Expectations, and treatment Effects (G-EEE): The questionnaire is used as a self-report instrument to assess the expectations for a treatment, pre-experiences, and treatment effects. The questionnaire will be applied to treatment with TMS in the present study.

Structured Clinical Interview for DSM-V (SCID): This is a common procedure for diagnosing mental disorders according to the DSM-V classification system of psychiatry [34]. It is to ensure that no relevant comorbidities are present.

Generic Assessment of Side Effects (GASE): This questionnaire assesses side effects [35] and will only be applied at T4 with the aim to record side effects that occurred during the course of the treatment.

Wechsler Adult Intelligence Scale (WAIS) IV Vocabulary Test: The vocabulary subtest of the WAIS IV [36] is designed to roughly estimate participants’ crystalline intelligence, i.e., acquired cognitive skills. The “vocabulary test” is the second core test of the index language comprehension. Individuals name objects presented as pictures or explain concepts presented orally or in writing. It measures a person’s vocabulary and concept formation.

Number Connection Test: This test [37] is a language-free intelligence test designed to roughly assess the cognitive flexibility of test participants.

Experimental computer-based test procedures for recording the success of the therapy: survey at two points in time, before and after the therapy.

Movie for the Assessment of Social Cognition (MASC): The MASC [38] is a well-validated instrument for assessing social cognition, in particular the ability to grasp the thoughts, feelings, and intentions of other people. As this ability is diminished in people with (chronic) depression [39–41] and the limitations in social cognition may themselves contribute to maintaining depressive symptomatology [42], social cognition is also an important measure of the success of sustained antidepressant treatment. To measure this, participants are shown a 15-min video of four friends meeting for dinner. The video is stopped a total of 46 times, so that the participants can answer questions about the situation presented. The participants have to consider different sources of information (language, facial expressions, gestures), and the sequences shown have different valences (negative/neutral/positive) and are of varying complexity (some questions require an understanding of sarcasm or metaphors, for example).

Trust game: In accordance with the reduced ability of depressed individuals to identify thoughts, feelings, and intentions in others, as described above, depression is thought to involve reduced emotional mimicry (i.e., imitating social cues of the other person with the goal of building trust) [43]. Based on the described deficits in emotion recognition, depressed patients also have more difficulties trusting other people [43]. Participants have to invest money in a virtual counterpart which either reflects the emotional expression of the participant or not. The outcome parameter is the investment behavior of the participants.

Emotion recognition task: This task aims at the reduced ability of depressive patients to recognize emotions in other people [40]. For this task, participants will be shown a selection of 140 photos of ten models (five women, five men). These are taken from the Karolinska Directed Emotional Faces [KDEF [44]], with each model showing seven facial expressions (happy, surprised, angry, sad, fearful, disgusted, and neutral) both frontally and in profile. In the task, participants are shown a facial expression for a duration of 700 ms, after which they must name the expression as accurately and quickly as possible, with responses and reaction times recorded as outcome parameters.

Biological parameters (neuroimmunology, (epi-)genetics): Survey at two time points (T1: before therapy, T4: after therapy).

Blood sampling: In total, less than 60 ml of blood will be taken. Plasma concentrations of C-reactive protein (CRP), interleukin (IL)-6, and tumor necrosis factor (TNF)-α as systemic inflammatory markers will be determined along with (epi)-genetic markers, e.g., acetylations.

Collection of saliva: Saliva samples will be self-collected by the study participants with commercial collection devices. This is a painless procedure that usually takes 60 s. The salivary cortisol awakening response will be used as a measure of the activity of the hypothalamic–pituitary–adrenal (HPA) axis. Hormone determinations will require three saliva samples taken on each of two consecutive days immediately, 30 and 45 min after awakening.

Parameters indicative of cerebellar dysfunction: survey at one time point before therapy (neurological examination and ataxia scores, see below).

Eyeblink conditioning: Delay conditioning paradigm will be used [16]. A tone will be used as the conditioned stimulus (CS) and an air puff directed to the outer canthus of the eye as the unconditioned stimulus (US). CS and US coterminate. Surface EMG recording of the orbicularis oculi muscles will be used to measure unconditioned (UR) and conditioned (CR) responses. The focus will be on the acquisition of conditioned blink reflex responses [16, 18]. Participants learn that the CS predicts the occurrence of the US and learn to close their eyes prior to the occurrence of the US. The CR incidence is the primary outcome parameter and will be determined using semi-automated analysis software. CR timing will also be assessed.

Imaging: Functional connectivity in resting state MRI and diffusion tensor imaging (DTI) before and after therapy.

MRI of the skull: The examination takes place in a 3 T scanner (Magnetom Vida, Siemens, Erlangen, Germany, 3 T) at the University Medical Center Essen (Institute for Diagnostic and Interventional Radiology).

Functional imaging–resting-state: fMRI allows indirect measurement of neuronal-related changes in brain metabolic activity (blood oxygenation level-dependent (BOLD) response). The advantages of the method include the recording of the activity of the entire brain in a few seconds, as well as the spatial resolution achieved in the process. During the rs measurement, the participants are not confronted with any tasks or stimulation beyond “lying quietly.”

Structural recordings: High-resolution, structural, T1-weighted recordings of the brain are required for the analysis of the fMRI data and are acquired using MP-RAGE sampling (or similar T1-weighted methods). Participants have no other tasks to perform during the examinations.

Diffusion tensor imaging (DTI): DTI sequences are applied to investigate structural connectivity in addition to predictors of expectancy effects at the level of functional connectivity. The measurement time for the complete protocol is approximately 30 min.

For the last four items (i.e., experimental computer-based test procedures, biological parameters, eyeblink conditioning, and MRI), the healthy control group is needed as explained in section “Trial design {8}”.

### Additional measures

Edinburgh Handedness Inventory: This is a short questionnaire designed to assess handedness [45].

### Participant timeline {13}

[figure not shown]

### Sample size {14}

Since no study with the same or similar content has been conducted to date, the case number calculation was based on a study by Claus et al. [7], who also investigated the expectancy effect with regard to antidepressant pharmacotherapy. In this study, the outcome was measured by the BDI and HRSD, CGI, SHPS, and Well-Being Questionnaire WHO-5 that showed effect strengths ranging from 0.79 to 1.6 (Cohen’s *d*; repeated-measures ANOVA, four time points, *α* = 0.05, 1 − *β* = 0.95, two groups). A case number calculation based on these effect sizes yielded a case number of *n* = 7 per intervention group. On the other hand, it must be emphasized at this point that in studies on antidepressant treatment, mostly small effect sizes are observed, which we do not want to disregard. To account for an effect size in the current study that is expected to be lower than the one in the work by Claus et al., the necessary sample size was estimated to be an *n* = 30.

As it is to be expected that due to the complex study protocol with several examinations at a total of four time points, about 10% of the data will be lost, at least 35 patients per group should be recruited.

### Recruitment {15}

Through the newly established Center for Treatment-Resistant Depression (*Zentrum für Therapieresistente Depressionen*) at the LVR-University-Hospital Essen, a large number of interested and/or referred patients present themselves for a consultation. Furthermore, a flyer was created that summarizes the content of the study to be distributed to psychiatric practices. In addition, a training event on the topic of therapy-resistant depression will be conducted to familiarize potential referring physicians with the study. The recruitment of the healthy control group is based on age, gender, and education of the patient group. For this purpose, the study team recruits control subjects from the professional and private environments. In addition, an appeal via social media is planned in case not enough participants are found via the first step. The recruitment period is scheduled for a period of 1 year.

### Assignment of interventions: allocation

#### Sequence generation {16a}

The participants are divided into two groups (intervention group versus control group) with an allocation ratio of 1:1 and *n* = 30 participants per group. Stratification by gender is performed to ensure a balanced gender ratio; beyond that, there are no other factors used for stratification. The freely available online software “randomizer” (randomizer.org; last access 8/15/2023) will be used for this purpose.

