### Trial design {8}

We are planning an interventional, monocentric, randomized, controlled trial with two MDD patient groups of 30 participants each.

Our study is of the parallel group type, i.e., we are looking at two groups of patients in parallel, with one group of patients receiving an intervention while the other one does not. The framework is “superiority”: we expect to see superiority in outcome parameters in the intervention group. The allocation ratio in the intervention versus the control group is 30:30.

As it is to be expected that about 10% of the data will be lost due to the complex study protocol with several examinations at a total of four time points, at least 35 patients should be recruited per group. This minimum recruitment number seems achievable based on our experience with previous studies. The details of the intervention are outlined below.

In addition, an age-, sex-, and education-matched control group of 30 participants will be recruited, who will serve as a control only for the additional experimental investigations, which is the MRI part and the eyeblink conditioning. In these two subprojects, the first step is to evaluate the changes in the context of depressive illness in general compared to a healthy control group, see the “Outcomes {12}” section.

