### Who will take informed consent? {26a}

During outpatient or inpatient treatment, potential study patients receive information about the possibility of participating in the study and are asked for permission to contact them by telephone if they are interested. In addition, interested patients who have learned about the study via the LVR-University-Hospital homepage or have received the flyer about the study via psychiatrists in a private practice can contact us via an e-mail address set up specifically for the study.

In the next step, potential participants receive further relevant information such as the time of participation and duration of the examinations via telephone. In this process, the inclusion and exclusion criteria are also systematically checked. If there are no contraindications up to this point, an appointment is made to see the investigator for an in-depth educational interview, and verbal as well as written informed consent to participate in the study is obtained.

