#### Strategies to improve adherence to interventions {11c}

Participation in the study offers patients the option of treatment with TMS, which is not yet routinely available at all clinical sites in Germany and which will also be offered independently of study participation in the inpatient setting. In the outpatient setting, however, treatment costs have not always been covered by health insurance in Germany up to now, so that participation in the study may enable patients to choose a more preferable form of treatment. In addition, very extensive psychometric testing is performed, which goes beyond the standard clinical practice and can provide patients with an indication of their current level of performance. Adherence, in the present study, consists of daily attendance at the clinic where TMS is performed, which can be tracked very easily.

As therapy adherence is certainly a major challenge in the study, and in order to take quality control into account, the complexity of the protocol will already be addressed during the first telephone contact, so that the participants can adjust accordingly. In the event that at this point there is already strong uncertainty regarding the realization of the study visits, the participants will be informed about alternative treatment options for depression which would be easier to implement.

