#### Relevant concomitant care permitted or prohibited during the trial {11d}

The aim is to ensure that during study participation, any existing drug and/or psychotherapeutic treatment is continued with as little change as possible. In the event of a relevant change during study participation, discontinuation must be discussed individually. Change of medication during the treatment is also not an exclusion criterion per se but will be recorded as an event that will need additional control.

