## Statistical methods

### Statistical methods for primary and secondary outcomes {20a}

Analysis of variance (ANOVA) with repeated measures is planned for the evaluation of the parameters of therapy outcome (questionnaires for depression), therapy expectancy (questionnaires see above), biological parameters, and tests for cerebellar function (neurological examination, ataxia scores, and blink reflex conditioning). In case of missing values, a linear mixed model analysis is planned. An unpaired *T*-test or chi-square test is planned to determine the group differences at a given point in time. Correlation analyses are planned to correlate parameters of therapy success with treatment expectations.

The MRI data will be analyzed using statistical parametric mapping (SPM, https://www.fil.ion.ucl.ac.uk/spm/; last access 8/15/2023): automated group comparisons in terms of *T*-test and ANOVA will be performed including covariates.

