Another difficulty is certainly the complex and in part very extensive study protocol, which not only might limit the number of study participants but can also amount to a considerable effort for patients suffering from depressive disorder. In order to accommodate the study participants, it is possible to distribute the examinations planned before the start of the study over several appointments. Nevertheless, this aspect, as well as the high frequency of treatment days, could discourage participants with long travel distances from participating in the study.

Despite this, the study offers the possibility to increase the availability of treatment with TMS, a comparatively new and not yet widely introduced treatment for therapy-resistant depression, also on an outpatient basis. Furthermore, the study should contribute to the understanding and treatment optimization of an individually very disabling and economically highly relevant disease.

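### Inpatients and outpatients are randomised together with gender as the only stratum, and the stated depression-scale analyses name neither setting, gender nor T1 score as a covariate

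*Protocol article*

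**What the plan says.** The protocol article draws on both care settings. Under Who will take informed consent {26a}: "During outpatient or inpatient treatment, potential study patients receive information about the possibility of participating in the study". Under Strategies to improve adherence {11c}, TMS is a treatment "which will also be offered independently of study participation in the inpatient setting", while "In the outpatient setting, however, treatment costs have not always been covered by health insurance in Germany up to now". The Discussion adds that the study can widen access to TMS "also on an outpatient basis".

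Trial design {8} plans a randomised trial "with two MDD patient groups of 30 participants each". Sequence generation {16a} fixes the stratification: "Stratification by gender is performed to ensure a balanced gender ratio; beyond that, there are no other factors used for stratification". Eligibility criteria {10} agrees that gender is the stratification factor.

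For the clinical scales, Statistical methods {20a} states: "Analysis of variance (ANOVA) with repeated measures is planned for the evaluation of the parameters of therapy outcome (questionnaires for depression". The same sentence goes on to the other outcomes. A linear mixed model replaces the ANOVA if values are missing (also {20c}), and arms are compared at a given time point by an unpaired t-test or chi-square test. No covariate is named for any of these. Covariates are mentioned once in the section, for the MRI group comparisons.

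On background care, Relevant concomitant care {11d} aims that "any existing drug and/or psychotherapeutic treatment is continued with as little change as possible".

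**The concern.** Setting is known before the envelope is opened and could predict the course of depression in several ways. Ongoing drug and psychotherapeutic treatment continues, so background care may differ between ward and clinic patients. Daily attendance and travel weigh more on outpatients. Entry allows moderate as well as severe episodes, which may be distributed differently between settings.

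With 30 per arm, chance can leave the arms unequal in setting. Stratification does not prevent this, so the analysis is the only place left to handle it, and the stated analyses have no term for it. They also omit gender, although gender is the stratification factor and a model should normally carry it. The single-time-point tests do not use the T1 score, which is likely to be the most informative entry variable. What is at stake is precision, and how far one realised comparison can be trusted, in a trial whose Discussion names its low case number as a possible weakness.

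**Working it through.** **Inputs.** From the protocol: 1:1 allocation, 30 per arm, 60 patients in all ({8}, {16a}). The protocol gives no figure on setting that could be reproduced. Two quantities are therefore assumed and varied: the inpatient share *p*, and the inpatient-outpatient difference in outcome *g*, in within-setting SDs.

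**1. Chance of imbalance.** With K inpatients among 60, the number X falling in one arm is hypergeometric (60, K, 30), and the arms differ by |2X − K|. A difference of 6 inpatients is 6/30 = 20 percentage points.

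| Inpatients K | Share | P(difference ≥ 6) |
|---|---|---|
| 6 | 10% | 2.4% |
| 12 | 20% | 10.4% |
| 20 | one third | 17.0% |
| 30 | half | 19.6% |

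For K = 6 this can be done by hand: 2 × C(30,6)/C(60,6) = 0.024. An imbalance of 30 points or more has probability of at most about 2% in the shares computed (20% to 70%).

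**2. Effect on an unadjusted single-time-point comparison.** The arm difference shifts by (imbalance) × *g*. The standard error without setting, relative to that with setting, is √(1 + p(1−p)g²). Power is shown for an illustrative d = 0.5, 30 per arm, two-sided 0.05, normal approximation. With setting in the model it is 49%. For p = 0.5:

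| g | Shift at 20 points | SE factor | Power without setting |
|---|---|---|---|
| 0.2 | 0.20 × 0.2 = 0.04 SD | √1.01 = 1.005 | 49% |
| 0.5 | 0.10 SD | √1.0625 = 1.031 | 47% |
| 0.8 | 0.16 SD | √1.16 = 1.077 | 44% |
| 1.0 | 0.20 SD | √1.25 = 1.118 | 41% |

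At p = 0.3 the SE factors are 1.004, 1.026, 1.065 and 1.100.

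**3. Type I error.** In simulations of 100,000 trials per scenario (g of 0.5 to 1.0, p of 0.3 or 0.5), the unadjusted t-test rejects in 4.95% to 5.18% of all null trials, and the estimate averages zero. Among trials that happen to have an imbalance of 20 points or more, it rejects in 6.8% (g = 0.5), 8.7% to 8.9% (g = 0.8) and 10.4% (g = 1.0). Balanced trials reject less often (4.3% at g = 0.5, 2.9% at g = 1.0, both at p = 0.5), and the two offset each other.

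**4. The group-by-time test.** The repeated-measures analysis includes T1. Suppose the settings differ by a constant amount at all four visits. That amount drops out of every change from T1 and lies in the between-subject part of the variance, outside this test's residual. Only a different course by setting enters. For this test, *g* in step 2 must be read as the difference in change between settings, and the severity gap at entry does not count.

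**The case against.** The strongest objection is that a protocol article commonly leaves the covariate list to the analysis plan, which is not shown, and that {20a} is silent on adjustment and does not exclude it. This has weight: covariates may be listed elsewhere. But {20a} does name specific unadjusted tests for single time points, and it attaches covariates to the MRI comparisons only. The gender-only stratification is a positive statement.

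Second, a reader might infer that setting is a strong prognostic factor here. The documents do not say so. Everyone meets the same entry criteria, receives the same TMS and attends daily, and {11d} records medication changes as events needing additional control. The inpatient share is also unknown. Some passages point to a mainly outpatient sample: inpatients can have TMS without joining, the cost incentive is outpatient, and recruitment uses consultations and practice flyers. At a 10% share a 20-point imbalance is rare, and at g = 0.2 the loss is negligible. These objections stand and limit the size of the point.

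Third, a reader might infer that the arm comparison is biased or its type I error inflated. Steps 3 and 4 show otherwise: overall error stays near 5%, and the main repeated-measures test already removes stable differences.

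Finally, chronicity or the number of failed drugs could be argued as covariates just as well. That is fair. Setting is proposed because the protocol itself describes two routes of care and access, and because it is recorded without effort.

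**Conclusion.** The point holds as a modest one about precision and pre-specification. The text supports three facts: both settings are randomised together, gender is the only stratum, and the depression-scale analyses as stated name no covariate. The unpaired single-time-point tests are the most exposed, because nothing in them uses the baseline.

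The cost of leaving setting out ranges from nothing noticeable to a 12% larger standard error, and a 20-point imbalance would shift a single-time-point difference by 0.04 to 0.20 SD. The upper ends require about half the sample to be inpatients (for the standard error) and a setting difference of a full SD (for both), neither of which the documents establish. For the group-by-time test the effect is smaller and depends on the settings having different courses. The documents do not support a claim of a biased estimate, of overall type I error above 5%, or of a faulty randomisation.

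**What to change.** In {20a}, analyse each depression scale with a mixed model for T2 to T4 containing arm, time and arm by time, with T1 score, gender and setting at randomisation (inpatient or outpatient) as pre-specified covariates. Replace the unpaired t-tests on these scales with ANCOVA using the same covariates. Report setting by arm in the baseline table.

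Two details matter. If T1 is instead kept among the outcomes, a main effect of setting does nothing for the group-by-time test, and setting must then interact with time. The T1 score must also be recorded before the envelope is opened and the consultation held. The visible text places T1 within two weeks before therapy but does not state this order, and the timeline figure is not shown.

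The cost is about one degree of freedom per covariate, and the setting term gains little if setting is only weakly prognostic. Recruitment began in June 2022, and nothing in the randomisation needs to change. Fixing the covariates before the data are analysed also avoids a post hoc decision if an imbalance appears.
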